## Methods

### Study Design

This study is a randomised, positive drug parallel-controlled, open-label, non-inferiority clinical trial in patients with glucose and lipid metabolism disturbances. In total, 96 patients diagnosed with T2DM and dyslipidaemia will be recruited for this study. The patients will be randomly divided into two groups and treated with the JTTZ recipe or metformin for 12 weeks. This study protocol follows the Standard Protocol Items: Recommendations for Interventional Trials. (Chan et al., 2013). (Supplementary File S1). The study flow is illustrated in Figure 1. All information related to the treatment schedule is presented in Table 1.

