### Sample Size

Based on a previous study, the HbA1c level generally reduced by 1.0 and 0.9% using metformin and JTTZF for treatment, respectively. (Zhao, 2013; China Diabetes Society, 2021). The sample size was calculated by assuming a test power of 80% and a confidence level of 95%, Z_1-alpha/2_ = 1.960, alpha = 5% for the two-tailed hypothesis, Z_1-beta_ = 0.842, sigma = 0.024. A total of 38 patients are required in each group. Allowing for a 20% dropout rate during the follow-up period, the sample size was increased to at least 48 patients for each group, thus, creating a total sample of 96 patients. PASS software (version 11.0; NCSS, LLC. Kaysville, UT, United States) was used for these calculations.

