### Primary Outcomes

The changes of HbA1c levels are the primary study outcomes Besides, the rates of effectively regulated HbA1c, FPG, 2 h-PG, TG, and LDL-C levels will be calculated based on the number of patients who make the target achievement. The HbA1c level ≤7%, FPG level ≤7.0 mmol/L (126 mg/dl), 2 hP G level ≤10.0 mmol/L (180 mg/dl), TG level ≤1.7 mmol/L (150 mg/dl), LDL-C level ≤3.3 mmol/L (130 mg/dl) will be set as the target achievement. The FPG levels will be tested during the screening period, before intervention, and every 4 weeks during the treatment period. The levels of HbA1c, 2 h-PG, TG, and LDL-C will be recorded during the screening period, at the beginning and at the end of the12-week treatment period.

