### Statistical Analysis

Intention-to-treat, per-protocol analysis, and the safety analysis will be performed. The per-protocol analysis will include only those patients who completed treatment and follow-up protocols in the allocated intervention group. Continuous variables (including age, disease duration, blood glucose, HbA1c) will be reported as means and standard deviations or as medians and interquartile ranges, as suitable. Categorical variables (including sex, past medical history, and previous treatment) will be reported as proportions. Continuous variables will be compared between the groups using analysis of variance and repeated measurement design will apply repeated-measure analysis of variance, including group and time-group interactions. The Wilcoxon rank sum test will be used to analyse non-normally distributed data. Count and grade data will be reported as frequencies (constituent ratio). Count data will be tested with the chi-square test or Fisher’s exact probability method, and grade data will be analysed using the Wilcoxon rank sum or Cochran-Mantel-Haenszel test. All statistical analyses will be performed using SPSS (version 24.0; IBM Corp., Armonk, NY, United States), and statistical significance will be set as two-sided *p*-values of ≤0.05.

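### The rank-sum fallback for non-normal data covers the primary HbA1c change, so the observed distribution decides whether a non-inferiority trial sized on means compares means or ranks

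*Protocol article*

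**What the plan says.** Study Design describes an "open-label, non-inferiority clinical trial in patients with glucose and lipid metabolism disturbances". Under Primary Outcomes, "The changes of HbA1c levels are the primary study outcomes". Sample Size uses expected HbA1c reductions of 1.0 (metformin) and 0.9 (JTTZ).

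Statistical Analysis lists HbA1c by name: "Continuous variables (including age, disease duration, blood glucose, HbA1c) will be reported as means and standard deviations", "or as medians and interquartile ranges, as suitable". Then: "Continuous variables will be compared between the groups using analysis of variance", with a repeated-measures version for repeated designs. The next sentence is the fallback: "The Wilcoxon rank sum test will be used to analyse non-normally distributed data". It names no criterion for non-normality and makes no exception for the primary outcome.

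Two other places matter. The section on removal and dropout says that a dropout's last record enters the analysis. Table 1 shows no HbA1c measurement between week 0 and week 12.

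**The concern.** Analysis of variance and the rank-sum test answer different questions. The first compares mean HbA1c change, the quantity on which the trial was sized. The second asks whether values in one arm tend to rank above those in the other. When the two arms differ in shape as well as location, the answers can diverge.

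Under the rule as written, the choice between them is made after the distribution of the primary outcome has been seen. A non-inferiority claim needs a statement of how much worse JTTZ could be, in HbA1c points. A rank-sum p-value does not supply one. At stake are the meaning of the primary result and, in some patterns of response, the chance of noticing a real deficit.

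**Working it through.** **1. The sample size is a comparison of means.** Inputs from Sample Size: difference 1.0 − 0.9 = 0.1; z-values 1.960 and 0.842; sigma 0.024. The figure of 38 is reproduced only if 0.024 is read as a variance:

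n per arm = 2 × (1.960 + 0.842)² × 0.024 / 0.1² = 2 × 7.851 × 0.024 / 0.01 = 37.7, rounded up to 38.

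With 20% dropout: 38 / 0.80 = 47.5, rounded up to 48. The implied SD is √0.024 = 0.155 points.

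**2. How likely is a switch?** The article names no trigger, so Shapiro-Wilk at 0.05 is assumed. With no HbA1c reading between weeks 0 and 12, a patient who leaves early has only a baseline value to carry forward, so the change is 0. With a mean change of −1.0 and SD 0.155, that value lies 1.0 / 0.155 = 6.5 SDs from the mean. Simulated switch rates at 48 per arm, mean change −1.0 in both arms:

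| Dropout, JTTZ / metformin | SD 0.155 | SD 1.0 (assumed) |
|---|---|---|
| 20% / 20% | 100% | 80% |
| 30% / 10% | 100% | 91% |
| 20% / 5% | 100% | 59% |

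These test each arm separately. Testing pooled within-arm residuals lowers the SD 1.0 figures, to about 74% at the lowest in the settings that average 20% dropout. The range of 74-100% therefore belongs to dropout near the planned 20%. In a further check (2,000 trials), 10% in both arms with SD 1.0 gave only about 25-31%.

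**3. What the switch does to the dropout case.** At 30% v 10% dropout the true mean difference is (0.30 − 0.10) × 1.0 = 0.20. With SD 0.155 the rank-based (Hodges-Lehmann) shift is 0.08, and rejection falls from 65% (t-test) to 39% (rank-sum). With SD 1.0 the order reverses: 17% (t-test), 21% (rank-sum).

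**4. A poorly responding JTTZ minority.** Assumed: metformin change normal, mean −1.0, SD 0.8; JTTZ the same except that 15% of patients end 2 to 3 points higher. The mean deficit is 0.15 × 2 = 0.30 up to 0.15 × 3 = 0.45. At 48 per arm:
- unequal-variance (Welch) test: detects the deficit in 33-49% of trials;
- the plan's rule: 25-29%;
- rank-sum alone: 22-24%.

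With SD 1.0 and a 3-point shift, the mean difference is 0.45 and the rank-based shift 0.30.

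**5. Other patterns, same size.**
- 15% ordinary non-responders (1 point worse, so no change from baseline): mean test 14%, rule 14%, switch in 6% of trials.
- A 0.45-point deficit shared by all JTTZ patients, with skewness 1.5 in both arms: mean test 77%, rule 90%.
- The same with heavy tails (t with 3 df): 81% and 95%.
- The same with 15% outliers of +3 in both arms: 37% and 51%.

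**6. Is the trigger directional?** With SD 1.0, 48 per arm and 15% shifted by 3 points, the switch rate is 63% if the minority does badly on JTTZ, 62% if it does badly on metformin, 62% if it does unusually well on JTTZ, and 84% if both arms have a poor minority. With both arms normal it is 10%.

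**7. Type I error.** With identical distributions in the two arms the rule rejects in 4.9-6.2% of trials (simulation SE √(0.05 × 0.95 / 2000) = 0.5 points). With equal means but different shapes (for example skewness 1.5 v 0.3, or 1.5 v −1.0) it rejects in about 6-14%, against 5-6% for the Welch test.

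**The case against.** The best defence is that parametric-or-rank wording is a common summary convention and that a condensed article may leave the criterion, and any exemption for the primary outcome, to the full protocol or SAP. The missing criterion is indeed no finding. What remains is a rule that is stated, is unqualified and covers HbA1c by name.

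The article also names no confidence interval or margin for the analysis-of-variance route, so their absence is not caused by the switch. That is correct. Analysis of variance does at least target the mean difference. A rank-based shift with an interval exists, but the article does not mention it, and it estimates a different quantity (0.30 against 0.45 in step 4).

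Four stronger readings are tempting, and the documents do not support them:
- That the switch is likeliest when a minority does badly on JTTZ. Step 6 shows it is symmetric.
- That ranks hide a deficit. They weaken it in some patterns and reveal it better in others. The loss in step 4 needs patients whose HbA1c rises by 1 to 2 points on treatment, and nothing in the article says this is typical.
- That the switch protects nothing. Under shared skew, heavy tails or outliers it gains power.
- That weight, waist and symptom scores lose their repeated-measures model. The rank-sum sentence does not say it replaces that model and may refer to simple two-group comparisons.

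**Conclusion.** The point holds as a defect in the target of the primary analysis. The data may decide whether HbA1c change is compared as means or as ranks, in a trial called non-inferiority and sized on means. After a switch, the planned result does not state how many points worse JTTZ could be.

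The switch is a realistic prospect: about 74-100% of simulated trials at 48 per arm with dropout averaging 20% (10-30% by arm) and SD 0.155-1.0, and less often with lower dropout. This assumes that dropouts leave before week 12 with only a baseline HbA1c. The planned 20% is described as occurring during follow-up and may include later losses.

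The effect on sensitivity has no fixed sign: a loss from 33-49% to 25-29% in the severe-minority case, none for ordinary non-responders, and a gain under shared skew, heavy tails or outliers. Inflation of the type I error is not established in general. It appears, at about 6-14%, only for chosen cases with equal means and different shapes. The SDs of 0.8 and 1.0, the minority sizes and shifts, the shapes and the Shapiro-Wilk trigger are all assumptions.

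**What to change.** Limit the rank-sum sentence and name one primary analysis. Suggested content: the change in HbA1c from baseline to week 12 is compared between groups as a difference in means with a 95% confidence interval, using an unequal-variance or robust standard error, whatever any check of normality shows. The rank-sum test is used for ordinal grade data and, for HbA1c change, as a labelled sensitivity analysis.

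The cost is one sentence in the analysis section, with no change to patients, visits or measurements. The downside is some loss of power if HbA1c change is skewed or heavy-tailed in both arms (for example 77% against 90% in step 5), which the sensitivity analysis would show. In simulations of the poor-minority pattern with 38-48 per arm, the mean-based 95% interval kept 94-95% coverage.

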## Abstract

**Background:** Type 2 diabetes mellitus (T2DM) complicated with dyslipidaemia is associated with a high risk of cardiovascular diseases. The Jiangtang Tiaozhi (JTTZ) recipe is a Chinese herbal formula that has been used to regulate the blood glucose and lipid levels for many years. Interestingly, a previous study has demonstrated its efficacy; however, the associated mechanism remains unclear. We hypothesised that the therapeutic effect of the JTTZ on patients with T2DM may be mediated by the modulation of metabolites secreted by the gut microbiota. This study aims to examine this mechanism.

**Methods and analysis:** This study is a randomised, positive drug parallel-controlled, open-label clinical trial in patients with T2DM and dyslipidaemia. A total of 96 patients will be recruited and randomly assigned to treatment with JTTZ or metformin for 12 weeks. The primary outcome will be the rates of effectively regulated blood glucose and lipid levels (measured with the levels of glycated haemoglobin, fasting plasma glucose, 2-h plasma glucose, triglyceride, and low-density lipoprotein cholesterol). The secondary outcomes will be the changes in body weight, body mass index, and waist circumference and Traditional Chinese Medicine symptom scores. In addition, 16S rRNA gene sequencing will be performed on the gut microbiota obtained from faeces, and metabolomics analysis will be performed based on blood and gut microbiota samples. Intention-to-treat, per-protocol analysis and safety analysis will be performed.

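### The five target-achievement rates are compared by an unadjusted chi-square or Fisher test although each marker's week-0 value is collected: a valid test that gives up some precision

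*Protocol article*

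**What the plan says.** The abstract states: "The primary outcome will be the rates of effectively regulated blood glucose and lipid levels". The Primary Outcomes section opens differently, with "The changes of HbA1c levels are the primary study outcomes", and then adds the rates for HbA1c, FPG, 2-h PG, TG and LDL-C, which "will be calculated based on the number of patients who make the target achievement". Each rate is therefore a count of patients at or below a fixed cut-off.

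For such counts the Statistical Analysis section says "Count data will be tested with the chi-square test or Fisher’s exact probability method". It names no covariate and no regression model for a binary outcome. The Cochran-Mantel-Haenszel test appears only as an option for grade data.

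Baseline values exist for all five markers. Primary Outcomes says "The levels of HbA1c, 2 h-PG, TG, and LDL-C will be recorded during the screening period, at the beginning" and at the end of treatment, and "The FPG levels will be tested during the screening period, before intervention, and every 4 weeks during the treatment period". Table 1 confirms a week-0 measurement of each. Previous treatment is also recorded, and the Interventions section lets earlier lipid-lowering drugs continue.

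**The concern.** Whether a patient ends below a fixed cut-off is likely to depend on how far above it that patient started. The entry criteria leave room for this. They set no limit on HbA1c, and the glucose criterion is met by FPG or by 2-h PG, so some patients can enter already at target on one of these markers. The planned test treats such a patient like one who starts far from target.

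If the baseline value predicts target achievement, ignoring it makes the interval for each rate difference wider than the collected data require. That matters with 38 evaluable patients per arm. The same holds for background lipid-lowering drugs and the TG and LDL-C rates.

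**Working it through.** **1. The plan's own figure.** Sample Size uses HbA1c reductions of 1.0 and 0.9 (difference 0.1), 80% power, "alpha = 5% for the two-tailed hypothesis" and sigma 0.024. With 0.024 read as a variance, n = 2 × (1.960 + 0.842)² × 0.024 / 0.1² = 37.7, so 38 per arm; 38 / 0.8 = 47.5, so 48 per arm and 96 in total. The figure reproduces on that reading. It concerns HbA1c change. The article gives no power calculation for the rates.

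**2. Assumed inputs.** The expected rates, the baseline to week-12 correlation (rho) and any margin are not stated, so all are assumed below. The per-arm sizes of 38 and 48 and the two-sided 5% level come from the plan.

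**3. Test of difference, rho = 0.5, no range restriction.** Simulation with 3,000 trials per setting: bivariate normal baseline and week-12 values, with the latter dichotomised to give the stated rates. The pooled z-test (equivalent to chi-square) is set against the standardised risk difference from a logistic model with baseline. A repeat with 4,000 trials per setting is in the last column.

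| n per arm | Rates | Unadjusted | Adjusted | Gain | Repeat |
|---|---|---|---|---|---|
| 38 | 40% v 70% | 75.5% | 83.8% | 8.3 | 75.4% to 83.2% |
| 38 | 50% v 75% | 63.1% | 71.5% | 8.4 | 61.0% to 70.1% |
| 48 | 40% v 70% | 85.1% | 90.4% | 5.3 | 84.9% to 90.6% |
| 48 | 50% v 75% | 72.9% | 79.3% | 6.4 | 72.1% to 79.4% |

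The variance of the rate difference fell by 11-18%. The gain was 2-4 points at rho = 0.3 and 10-17 at rho = 0.7. Type I error at equal 50% rates was 5-6% for both methods.

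**4. Closed-form check.** Adjusted power = Φ((z_power + 1.96) / √(1 − r_b²) − 1.96), where r_b is the correlation of baseline with the binary outcome. At a 50% rate and rho = 0.5, r_b = 0.5 × 0.798 = 0.399 and r_b² = 0.159. From 80% power: (0.842 + 1.96) / √0.841 − 1.96 = 1.10, which gives 86.3%. Simulated likelihood-ratio and Wald tests from the logistic model, at settings with about 80% chi-square power, gave 86-88% with type I error of 4.6-5.6%. In the same settings Fisher's test had about 73-75%.

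**5. Range restriction.** Entry requires LDL-C ≥3.4 and TG >1.7 mmol/L, and FPG 7.0-13.9 or 2-h PG ≥11.1 mmol/L. If rho = 0.5 holds before selection and a floor sits at the population mean, the baseline variance shrinks by the factor 1 − 2/π = 0.363. Then rho becomes 0.5 × √0.363 / √(0.75 + 0.25 × 0.363) = 0.33. At a 50% rate r_b² = (0.33 × 0.798)² ≈ 0.07. Simulation at 48 per arm moved power from 79.9% to 82.4-82.9%. Over the settings examined the gain was 5-7% in variance and 2-5 points of power.

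**6. Non-inferiority, equal 50% rates.** Power = Φ(M / SE − 1.96), with SE = √(2 × 0.25 / n) and the adjusted SE multiplied by √0.89 to √0.82. The margins M are assumed. Example: n = 38 and M = 0.10 give SE = 0.1147 and Φ(0.872 − 1.96) = 13.8%.

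| Margin | 38 per arm | 48 per arm |
|---|---|---|
| 10 points | 13.8% to 15.0-15.9% | 16.3% to 17.8-19.0% |
| 15 points | 25.7% to 28.3-30.3% | 31.2% to 34.4-36.8% |
| 20 points | 41.4% to 45.5-48.6% | 50.0% to 54.7-58.1% |

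The gain is about 1-8 points here, and nearer 0 at the small margin if the range is also restricted.

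**The case against.** The strongest reply is that nothing here is an error. Under randomisation the unadjusted test is valid, and covariate sets are commonly left to an analysis plan. The first part stands: this is lost precision, not bias. The second stands only in part, because the article does more than stay silent. It names the test for count data, and that test takes no covariate.

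A second reply is that power for a difference is the wrong yardstick. Study Design calls the trial non-inferiority, and the planning reductions are nearly equal (1.0 and 0.9). Gaps of 25-30 points in the rates appear nowhere in the article. This stands. For non-inferiority the gain is smaller, and at margins of 10-20 points the rates stay underpowered either way. Adjustment does not rescue that comparison.

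Third, a reader might apply the 5-9 points to all five rates. The documents do not support this: both lipid markers have entry floors, glucose has partial ones, and only HbA1c has none.

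Fourth, a reader might infer that randomisation is unstratified, so that chance imbalance goes uncontrolled. The Randomisation section gives the procedure, the 1:1 ratio and concealment, and is silent on stratification. The argument does not need it.

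Fifth, the rates might be taken as the trial's sole primary outcome. The Methods name HbA1c change first and size the trial on it. The point covers the rates only; the mismatch between abstract and Methods is a separate matter.

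**Conclusion.** The point holds as a modest efficiency loss on outcomes that the abstract calls primary. With a baseline to week-12 correlation of 0.5 and no range restriction, adjustment saves about 11-18% of the variance of the rate difference, equal to about 12-22% more patients (1/0.89 = 1.12; 1/0.82 = 1.22). That is worth roughly 5-9 points of power for a difference of 25-30 points. Where entry floors truncate the baseline at its mean, the saving is about 5-7% of variance and 2-5 points. For non-inferiority with equal rates and margins of 10-20 points it is about 0-8 points. HbA1c is the marker most likely to sit at the upper end, and LDL-C and TG at the lower. The correlation, rates and margins are all assumptions; the direction of the gain does not depend on their exact values as long as baseline predicts target achievement.

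**What to change.** For each target rate, make the main analysis a logistic regression with arm and the week-0 value of that marker, adding baseline lipid-lowering drug use (yes/no) for TG and LDL-C. Report the standardised (marginal) risk difference with its 95% confidence interval. Such an interval can be set against a non-inferiority margin once one is stated, which a chi-square p-value cannot. Keep the chi-square or Fisher test as a sensitivity analysis, and name it in advance as the fallback if a model does not converge, for example when very few patients in an arm reach or miss a target.

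The change is to analysis wording only; no new data or patients are needed. It costs a little more analysis work. The plan names SPSS 24.0, and the standardised risk difference may need other software, such as the SAS already used for the randomisation list.

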**FIGURE 1 F1:**
[figure not shown]
Flow diagram of the study design.

**TABLE 1 T1:** Schedule of enrolment, assessments, and data collection.

Period	Enrolment/Baseline	Allocation	Treatment period			Follow-up period
Time points	Introduction period	0week	4 weeks	8 weeks	12 weeks	48weeks
Eligibility screening	×	—	—	—	—	—
Informed consent	×	—	—	—	—	—
Physical Examination	×	×	—	—	—	—
Characteristic	×		—	—	—	—
Random allocation	—	×	—	—	—	—
Interventions	—	—	×	×	×	—
Clinical Assessments	—	—	×	×	×	—
Medical history	×	×	×	×	×	×
Body weight	×	×	×	×	×	—
Waist circumference	×	×	×	×	×	—
Body mass index	×	×	×	×	×	—
Electrocardiogram	—	×	—	—	×	—
Routine urinalysis	—	×	—	—	×	—
Complete blood count analysis	—	×	—	—	×	—
HbA1c	—	×	—	—	×	×
FPG	×	×	×	×	×	×
2 h-PG	×	×	—	—	×	×
Blood lipid indicators	×	×	—	—	×	×
TCM symptom score	×	×	×	×	×	×
Liver and kidney function	—	×	×	×	×	—
Islet function	—	×	—	—	×	×
Urinary microalbumin	—	—	—	—	—	×
Urinary microalbumin/-creatinine ratio	—	—	—	—	—	×
Cardiac ultrasound	—	—	—	—	—	×
Carotid artery ultrasound	—	—	—	—	—	×
Biological specimens	—	×	—	—	×	—
Adverse event	—	×	×	×	×	—

FPG, fasting plasma glucose; PG, plasma glucose; TCM, traditional Chinese medicine.

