#### Diagnostic Criteria of Dyslipidaemia

The diagnostic criteria of dyslipidaemia are based on the *Chinese Guidelines on Prevention and Treatment of Dyslipidaemia in Adults* (2016, revision edition) (Chinese Joint Committee for Developing Chinese Guidelines on Prevention and Treatment of Dyslipidemia in Adults, 2016) and include any of the following: total cholesterol (TC) level ≥6.2 mmol/L (240 mg/dl), LDL-C level ≥4.1 mmol/L (160 mg/dl), high-density lipoprotein cholesterol level <1.0 mmol/L (40 mg/dl), and triglyceride (TG) level ≥2.3 mmol/L (200 mg/dl).

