#### Inclusion Criteria

Patients are eligible for this study if they meet the following criteria: 1) age of 18–70 years at the time of enrolment; 2) diagnosis of T2DM plus 7.0 mmol/L (126 mg/dl) ≤ FPG level ≤13.9 mmol/L (250 mg/dl), or 2-h PG level ≥11.1 mmol/L (200 mg/dl) at the time of enrolment; 3) diagnosed with dyslipidaemia plus LDL-C level ≥3.4 mmol/L (130 mg/dl) and having TG level >1.7 mmol/L (150 mg/dl) at the time of enrolment; 4) have a body mass index ≥24.0 kg/m^2^ or waist circumference ≥90 cm for men and ≥80 cm for women; 5) failure to take anti-diabetic drugs regularly to reach normal blood glucose and lipid levels after diet control and exercise therapy before enrolment; 6) TCM syndrome differentiation as excess heat in the stomach and intestines syndrome; and 7) provision of signed informed consent form.

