### Interventions

Patients in the JTTZ recipe group will receive the JTTZ recipe granules (30 g per bag), one bag at a time, twice a day, to be taken with warm water after meals. Patients in the metformin group will receive 500 mg metformin tablets at a time, three times a day, to be taken with meals. The allocated interventions may be modified. In addition, this study applies the add-on therapy and the former administration of lipid-lowering agents will not be withdrawn. If AEs or voluntary withdrawal occurs, the interventions will be discontinued. Laboratory tests and drug packing return will be arranged to monitor and improve adherence.

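### The LDL-C and TG target rates are compared by a valid but unadjusted chi-square or Fisher test; adjusting for the week-0 lipid value already collected would be a cheap, modest gain

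*Protocol article*

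**What the plan says.** All references are to the protocol article.

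- **Test.** Statistical Analysis: "Count data will be tested with the chi-square test or" Fisher's exact method. No covariate is named for this comparison.
- **Outcome.** Under Primary Outcomes, the rates of controlled HbA1c, FPG, 2-h PG, TG and LDL-C "will be calculated based on the number of patients who make the target achievement". The lipid targets are TG at most 1.7 and LDL-C at most 3.3 mmol/L. Neither Primary Outcomes nor Secondary Outcomes names a continuous lipid endpoint, so these two rates are the only lipid efficacy comparisons named there.
- **Baseline.** Primary Outcomes says the levels of HbA1c, 2-h PG, "TG, and LDL-C will be recorded during the screening period, at the beginning and at the end" of the 12 weeks. In Table 1, the row "Blood lipid indicators" is marked at the introduction period and at weeks 0, 12 and 48.
- **Entry range.** Inclusion Criteria asks for patients "diagnosed with dyslipidaemia plus LDL-C level" of at least 3.4 mmol/L and TG above 1.7 mmol/L. No upper limit is set for either lipid.
- **Dropout.** The section on removal and dropout enters a dropout's last record into the analysis. Sample Size allows for 20% dropout.

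**The concern.** Every patient is off both lipid targets at enrolment, but some are just above the cut-off and others far from it. If the starting value predicts who reaches the target, an unadjusted comparison of two proportions treats unlike patients as interchangeable. It then loses some power and leaves any chance imbalance in starting lipids uncorrected. Randomisation and Allocation names no stratification by lipid level, so balance on it is left to chance. The covariate needed is already scheduled, so the question is how much the named test gives up.

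**Working it through.** **1. The plan's own figure.** The only stated sample-size calculation is for HbA1c change. With difference 1.0 - 0.9 = 0.1 and 0.024 read as a variance, n = 2 × (1.960 + 0.842)² × 0.024 / 0.1² = 37.7, so 38 per arm. Then 38 / 0.8 = 47.5, so 48 per arm and 96 in total. This reproduces the plan, but says nothing about the lipid rates, for which the article gives no expected rate. Everything from step 3 on therefore rests on assumed inputs.

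**2. Distance from target.** The required fall is (baseline - target) / baseline. The middle row uses the diagnostic limits, which "include any of the following: total cholesterol (TC) level", LDL-C, HDL-C or TG criterion. The 5.0 and 4.0 in the last row are illustrations.

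| Starting point | LDL-C to 3.3 | TG to 1.7 |
|---|---|---|
| Near the entry limit | 0.1/3.4 = 3% | 0.1/1.8 = 6% |
| Diagnostic limit | 0.8/4.1 = 20% | 0.6/2.3 = 26% |
| Higher value | 1.7/5.0 = 34% | 2.3/4.0 = 58% |

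**3. Power with complete data.** Assumed: 48 per arm, control rate 30%, treatment odds ratio 3 given baseline, two-sided 5%, 20,000 simulated trials per setting. The test is the Wald test from a logistic model with treatment and week-0 value.

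| Baseline OR per SD | Chi-square | Logistic | Change, normal baseline | Change, skewed baseline |
|---|---|---|---|---|
| 1 | 75.0% | 74.5% | -0.5 | -0.4 |
| 1.5 | 72.0% | 73.2% | +1.2 | +0.6 |
| 2 | 65.7% | 69.5% | +3.8 | +2.9 |
| 3 | 55.5% | 63.9% | +8.4 | +5.7 |

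A separate simulation of the normal case gave -0.3, +1.2, +3.2 and +7.6 points.

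**4. Power under the article's dropout rule.** No lipid is measured between week 0 and week 12. A patient who leaves in between is analysed on a week-0 record that, short-term fluctuation aside, is above target. Such a patient counts as a failure whatever the baseline, which dilutes the covariate. Setting a random 20% to failure (all planned dropout before week 12, the upper end) and otherwise keeping step 3:

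- normal baseline: -1.0, -0.1, +1.5, +3.8 points in one simulation and -1.3, -0.2, +1.7, +3.9 in another;
- skewed baseline: -1.2, -0.1, +0.8, +2.4 points.

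Less early dropout gives results between steps 3 and 4.

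**5. Which baseline odds ratio is plausible.** With s = ln(OR)/1.7, the implied week-0 to week-12 correlation is s/√(1 + s²). For OR 3, s = 0.646 and the correlation is 0.54; for OR 2 it is 0.38; for OR 1.5 it is 0.23. The entry limits truncate the baseline and so lower the correlation. If a normal distribution were cut at its median (an assumption), correlations of 0.5, 0.6 and 0.7 would become 0.33, 0.41 and 0.51. That lies mostly near OR 2 or below.

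**6. Error rate and interval.** With complete data, type I error is 4.9 to 5.5% for chi-square and 4.6 to 5.0% for the Wald logistic test. With no treatment effect, the 95% CI half-width for the risk difference is 18.1 points unadjusted. Standardised from the logistic model it is 18.1, 17.8, 17.3 and 16.4 points at OR 1, 1.5, 2 and 3. Coverage is 94 to 95% for both.

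**7. Scale of the estimate.** Adjustment does not shrink the standard error of the log odds ratio. In a second simulation (38 per arm, 30% against 50%, correlation 0.5) it rose from 0.484 to 0.543, while the estimate moved from 0.87 to 1.03 and power from 0.431 to 0.499. The gain in precision shows on the risk-difference scale.

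**The case against.** The strongest case against is that nothing here is wrong. Chi-square and Fisher tests are standard for a responder rate and valid under randomisation. The article condenses a full protocol, and an analysis plan that is not shown may add adjusted models. That fixes the weight of the point: it is optional. It does not remove it, because the article names a method for these data and a better use of the same data is available.

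The second objection is size. The complete-data gains ignore the article's own rule for dropouts, and with 20% early dropout they are roughly halved or vanish. The upper end also assumes a strong association in a population already truncated by the entry limits. Both objections stand, and the conclusion is scaled to them.

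Third, the trial is declared an "open-label, non-inferiority clinical trial in patients with glucose and lipid metabolism disturbances", so power for a superiority effect of 30% to about 56% (odds 0.429 × 3 = 1.286; 1.286/2.286 = 56%) is not the most natural yardstick. Interval width is closer to the purpose, and there the gain is 0 to 1.7 points of half-width with complete data.

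A reader might infer three stronger claims that the documents do not support:

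- **That the named test inflates false positives.** With complete data, arm means differ by 0.3 SD or more in about 14% of trials, and chi-square false positives in those trials are 5.3, 5.9, 7.4 and 10.2% at OR 1, 1.5, 2 and 3. These rates are conditional on imbalance; over all trials the rate is about 5%.
- **That the plan withholds an interval for the difference in rates.** The article does not say so, and such detail is commonly left to the full protocol or analysis plan.
- **That background lipid therapy must also be a covariate, because** "the former administration of lipid-lowering agents will not be withdrawn". How far it predicts the outcome is unknown, since users and non-users alike enter off both targets. The documents do not support adding it.

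**Conclusion.** The point holds as an optional improvement in efficiency. The stated test is valid but does not use the week-0 lipid value that the trial already collects. Under the assumed inputs, adjustment changes power by about -0.5, +1, +3.5 and +8 points with complete data, and by about -1, 0, +1.5 and +4 points if 20% leave before week 12 and are carried forward as failures (baseline odds ratio 1, 1.5, 2, 3 per SD). The lower to middle part of that range is the more plausible. The control rate, the treatment effect and the strength of the baseline association are assumptions; the documents give none of them. What does not depend on them is that the covariate is scheduled for every patient, that the adjusted test keeps the error rate near 5%, and that the downside is small.

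**What to change.** In Statistical Analysis, state before the data are analysed that each lipid target rate is compared by a logistic model with treatment and the week-0 value of that lipid. Report the standardised risk difference with a 95% CI, and keep the chi-square or Fisher test as a sensitivity analysis. Do not add lipid-lowering drug use. The same model can serve the HbA1c, FPG and 2-h PG target rates, each with its own week-0 value, since Table 1 schedules all three at week 0.

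The cost is one or two sentences, with no extra visit, sample or patient. The downside is about 1 point of power if the week-0 value turns out not to be prognostic.
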